#### Overall functioning

Outcome Rating Scale (ORS): The ORS [26] will be used to assess functioning across different areas of the child’s life. It comprises four simple rating scales in which the parent rates how their child has been feeling over the last week (individually, interpersonally, socially, and overall wellbeing). Each item is rated using a 10-cm visual analogue scale, with instructions to place a mark on each line. A higher score indicates better functioning. It has good reliability and validity [27]. The ORS will be completed at baseline and then at 14 and 26 weeks-post randomisation by the parent.

#### Common comorbid emotional and behavioural problems

Strengths and Difficulties Questionnaire-parent report (SDQ-P): The SDQ-P [28] is a behavioural screening questionnaire. It comprises 5 scales assessing emotional symptoms, conduct problems, hyperactivity/inattention, peer relationship problems, and prosocial behaviour. It has satisfactory reliability [29, 30] and good concurrent and discriminant validity [31, 32]. The parent-report version will be completed at baseline and then at 14 and 26 weeks-post randomisation.

#### COVID-19-specific worries

Pandemic Anxiety Scale (PAS): The PAS [33] is a parent report 7-item scale designed to capture specific aspects of the COVID-19 pandemic that are provoking anxiety in the child. It comprises two factors: disease anxiety (e.g. catching, transmitting the virus) and consequence anxiety (e.g. impact on economic prospects). An initial evaluation of the scale indicates that the PAS is a reliable and valid parent report measure about their child [33]. The PAS will be completed by the parent at baseline and then at 14 and 26 weeks post-randomisation.

#### Health economic measures

EQ-5D (5L) (parent self-report): The EQ-5D (5L) will be used to assess parent’s quality of life [34]. It is a well-validated measure of health-related quality of life, designed to estimate quality-adjusted life years (QALYs), that is widely used across disease areas. It contains five questions, each related to a different domain of everyday life (mobility, self-care, usual activities, pain/discomfort, anxiety/depression). For each domain, the respondent has to indicate whether they experience no problems, slight problems, moderate problems, severe problems, or extreme problems. It also includes a visual analogue scale (VAS) for participants to rate their overall health on a scale from 0 (“worst imaginable health”) to 100 (“best imaginable health”). The respondent’s answers provide a description or profile of the respondent’s quality of life, and a weight or value can then be placed on each profile using an existing UK tariff derived from the general public [35–38]. The Eq-5D-5L will be completed at baseline and then at 14 and 26 weeks post-randomisation by the parent.

CHU-9D-proxy version (parent report on child): The CHU-9D is a paediatric measure of health-related quality of life, which allows the calculation of QALYs for use in cost-utility analysis. It includes nine dimensions (worried, sad, pain, tired, annoyed, schoolwork, sleep, daily routine, activities) each with five levels and has been validated in child and adolescent populations [39]. Parents will complete the proxy version at baseline and then at 14 and 26 weeks post-randomisation.

The Child Anxiety Impact Scale-parent report (CAIS-P) is the primary clinical outcome, but will be used also in the economic analyses. It captures the degree to which anxiety is interfering in the child and family’s life, measured at 26 weeks post-randomisation (see above).

Client Services Receipt Inventory (CSRI)—children’s version (parent report): A modified version of the CSRI [40] will be used to collect information on patient-level resource use for both children (parent-report on children) and parent (self-report). Parents will be asked to report use of health, social care and non-NHS services, medications, and parental time off work, school, and leisure activities at baseline (based on the prior 3 months) and then at 14 and 26 weeks post-randomisation. Parents will be provided with health diaries to facilitate recall of parent and child’s resource use.

Therapist Economic Logs (Supervision Logs and Treatment Logs): We will collect economic logs from therapists during the treatment phase (up to 26 weeks if applicable; in the C-TAU arm where there is no set end point to the treatment). Therapists in both trial arms will be asked to complete an economic log throughout treatment, to record all staff-time spent on treatment-related activities (e.g. training and supervision, preparation of sessions, administration, phone contact with parent, video-contact with child whenever applicable).

#### Treatment credibility and experience

Credibility and Expectation of Improvement Scale (CEI): Parents will be asked to complete the CEI to assess participant expectations and views regarding treatment credibility, after randomisation and prior to treatment commencing [41]. It consists of three items, rated on a scale from 0 ‘not at all’ to 10 ‘completely’, asking about how logical the treatment seems, confidence in its success at reducing their symptoms, and their likelihood to recommend the therapy to a friend with similar symptoms. This measure is administered after randomisation with reference to the allocated treatment arm.

An adapted version of the CEI will also be administered 14 weeks post-randomisation, to give a retrospective account of treatment credibility (i.e. the questions are reworded to be considered in light of having received treatment).

We have also adapted the CEI to evaluate therapists’ experiences of treatment within this trial. This comprises items referring to how logical they found the treatment, how comfortable they felt delivering the treatment, how prepared they felt, certainty in the success of the intervention, confidence recommending the treatment to other therapists, and likelihood of administering the treatment again. Completion of this is part of their delivery of the research study.

#### Adverse events reporting opportunity

Trial therapists will be asked to report any adverse events that they become aware of while working with families in either arm over the whole treatment period. We will also provide parents and children an opportunity to describe any negative impacts of participating in the study after completing the questionnaires at 14 and 26 weeks and, for participating parents, after completing the qualitative interview. So as not to ‘lead’ answers, we will enquire about both the positive and negative consequences of taking part in the treatment. The research team will regularly review responses to identify any responses that indicate the presence of an adverse event.

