#### Adverse event measures

Clinicians are requested to monitor and report any harms and adverse events during the treatment phase. Additionally, parents and children are given the opportunity to report any negative impact of participating in the study as part of the 14- and 26-week post-randomisation assessments, using a self-report form.

See below for more detail on the measures.

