#### Potential serious adverse events (SAEs) (to parent/child)

Admission to a psychiatric hospital (parent/child).Sectioned under the Mental Health Act.Significant and sustained deterioration of pre-existing mental health condition that requires immediate intervention that cannot be accommodated within the treatment protocol (as determined in clinical supervision).Diagnosis of new mental health condition.Suicidal behaviour.A serious safeguarding issue is revealed.

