#### Potential serious adverse events (SAEs) not directly related to the trial and adverse events (AEs)

Children’s schooling or parent/guardians’ work is adversely affected (e.g. due to time spent in therapy or assessments encroaching on school or homework time).One or more aspect of the therapy or assessment procedure induces unacceptable levels of distress for either the participant, their parent/guardian, or the therapist.It becomes apparent that one or more of the exclusion criteria is met (or inclusion criteria not met) by the participant. [NB. This will be logged but the participant remains in treatment as long as clinically appropriate and retained in the intent to treat sample.]A sustained and significant increase in detrimental behaviours (e.g. safety-seeking behaviours) as determined by any of the outcome measures collected throughout the study.The emergence of new detrimental behaviours (e.g. self-harm).Drop-out of treatment/request to change therapist (all routinely monitored for the presence of AEs).A complaint is received from a participant, their parent/guardian, or the therapist referring to an actual or perceived adverse event as defined above.

The window for reporting SAEs and AEs will be:(i)During the treatment phase based on therapist report(ii)Up to the end of study based on parent report (i.e. up to the 26-week assessment or qualitative interview, whichever is later).

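### Outside the treatment phase, families are asked about harms from taking part, while the protocol counts adverse events whatever their cause, so some listed events may be missed.

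*Protocol article*

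**What the plan says.** *Adverse event measures* states that at 14 and 26 weeks "parents and children are given the opportunity to report any negative impact of participating in the study", on a self-report form. *Adverse events reporting opportunity* repeats this ("We will also provide parents and children an opportunity to describe any negative impacts of participating in the study after completing the questionnaires") and adds, as a way of not leading the answers, that "we will enquire about both the positive and negative consequences of taking part in the treatment".

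Therapists have a broader brief: "Trial therapists will be asked to report any adverse events that they become aware of while working with families in either arm". The two reporting windows at the end of the section on potential SAEs and AEs are "During the treatment phase based on therapist report" and "Up to the end of study based on parent report", the latter closing at the 26-week assessment or the qualitative interview, whichever comes later.

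*Definition of serious adverse events* defines seriousness by the nature of the event, with no condition on cause. The list of potential SAEs begins with "Admission to a psychiatric hospital (parent/child") and goes on to sectioning, a new mental health diagnosis and suicidal behaviour. *Reporting procedures for adverse events/serious adverse events* commits the team to logging every AE and SAE, and makes relatedness a matter for the Chief Investigator's opinion.

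The paragraph after the reporting windows describes the 14- and 26-week opportunity differently: as one to report adverse events, anonymously, with no reference to the study as cause. It adds that the functioning and quality-of-life questionnaires will yield information on some potential adverse events.

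**The concern.** A question about the impact of taking part asks the respondent to judge causality before answering. A parent whose child is admitted to hospital for reasons they regard as unconnected with the trial can truthfully answer that there was no negative impact. The event is nevertheless on the protocol's SAE list, and the Chief Investigator was meant to judge its relatedness.

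At stake are the completeness of the harms data and their comparability between arms. The primary CAIS-P estimate is not affected. The trial does, however, compare a lower-contact online treatment with usual care and has no separate data monitoring committee. The Trial Steering Committee is to receive summaries of these family responses, so how they are elicited matters.

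**Working it through.** The plan gives no figure on this point to reproduce. The check compares the sections and then asks how long parent report stands without the therapist.

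**1. What is in scope against what is asked**

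| Element | Tied to the study as cause? | Source |
|---|---|---|
| SAE definition | No | *Definition of serious adverse events* |
| Listed SAEs (admission, sectioning, new diagnosis, suicidal behaviour) | No | *Potential SAEs (to parent/child)* |
| Listed AEs | Mixed: distress caused by therapy is tied to it; newly emerging self-harm is not | *Potential SAEs not directly related to the trial and AEs* |
| Recording | No; relatedness is judged later by the Chief Investigator | *Reporting procedures* |
| Therapist report | No, but treatment phase only | *Adverse events reporting opportunity*; reporting windows |
| Family question | Yes | *Adverse event measures*; *Adverse events reporting opportunity* |
| Family question, second description | No; anonymous | Paragraph after the reporting windows |

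The last two rows describe one opportunity in two ways. Only the second fits the scope set by the rows above them.

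**2. Time resting on parent report, on-schedule OSI course**

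Inputs: seven weekly sessions and a review four weeks after the last (*Intervention description*); start no later than 12 weeks after randomisation (*Participant timeline*); follow-up to 26 weeks.

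- First to seventh weekly session: 7 − 1 = 6 weeks. Adding the review: 6 + 4 = 10 weeks of treatment.
- Time outside treatment: 26 − 10 = 16 weeks; 16/26 = 62%.
- Start at week 0: 0 weeks before and 16 after. Start at week 12: 12 before and 26 − 22 = 4 after. The total is 16 either way.

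The schedule may be adjusted by parents or clinicians, so 16 weeks applies only to a course that runs to plan.

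**3. The same quantity in C-TAU**

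If C-TAU treatment occupies T weeks of the 26, parent-only time is 26 − T. *Health economic measures* says C-TAU has no set end point and that therapist logs may run up to 26 weeks. T is therefore not fixed: T = 26 gives 0 weeks, T = 10 gives the same 16 weeks as OSI, and T below 10 gives more than 16. A C-TAU start at week 12 leaves at most 14 weeks of treatment inside the window, hence at least 12 weeks outside it.

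**4. Other routes**

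- Outcome questionnaires: the protocol itself claims only some events for them.
- Drop-outs and requests to change therapist are monitored for AEs, and complaints that indicate an event are logged. Neither depends on the family question, but each needs a drop-out, a request or a complaint to set it off.
- CSRI: "Parents will be asked to report use of health, social care and non-NHS services, medications", at 14 and 26 weeks, for child and parent, without reference to the study. It would be expected to show admissions, although its items are not given. It appears under health economics and is not named as a safety source.

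**The case against.** The strongest reply is that the form is not shown. The schedule of assessments calls it an AE self-report, and one paragraph describes it as reporting adverse events without qualification. The actual items may already be cause-neutral, and item wording is something an article may leave to the full protocol. The open, balanced question also has a stated reason. Families can volunteer unrelated events, and the research team reviews the responses. Expedited reporting to the ethics committee concerns only related and unexpected SAEs.

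Much of this stands, and it limits the point to what may be missed. It does not remove the conflict, because the article itself gives the attribution framing in two places.

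A reader might infer three stronger conclusions that the documents do not support:

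- *That this question is the only safety collection outside treatment.* The questionnaires, drop-out monitoring and complaints are further, partial routes.
- *That SAE counts will be too low by some calculable number.* The documents give no event rate, saying only that the risk is very low, and nothing on how often families would attribute an event to the study. The 62% cannot be applied to the whole sample, since about half are in C-TAU.
- *That the bias favours OSI.* If C-TAU treatment runs longer, therapist reporting lasts longer there and OSI events are more easily missed. If OSI families more readily attribute events to an unfamiliar online programme, the effect runs the other way.

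**Conclusion.** The concern holds as an inconsistency with a practical consequence. The family question, as described in two sections, is narrower than the events the protocol undertakes to record, and a third description of the same opportunity does not match it. Listed events that a family does not link to the study may be missed before treatment begins or after it ends. About 16 of 26 weeks are exposed for an on-schedule OSI course; the C-TAU figure depends on an unstated treatment length. Completeness may therefore differ by arm, in a direction that cannot be settled from the documents.

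This assumes that the form follows the wording of the two sections that describe its content. If the form already asks about events regardless of cause, only the text needs correcting. The matter should be put right for the harms comparison; it does not bear on the non-inferiority conclusion for CAIS-P.

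**What to change.** 1. Reconcile *Adverse event measures* and *Adverse events reporting opportunity* with the definitions, lists and reporting procedures, so that the family report covers the listed events irrespective of perceived cause.
2. Keep the open question. Add a few yes/no items to the 14- and 26-week parent forms on the listed events since the last assessment: hospital admission, sectioning, suicidal behaviour, self-harm, new diagnosis.
3. Put these items in a part of the form linked to the participant ID. Anonymous answers cannot be followed up, judged for relatedness, or counted under the protocol's rule that an AE reported more than once for a participant is treated as an SAE.
4. Check admissions reported on the CSRI against the AE/SAE log in both arms, and pass any unmatched event to the existing procedure.

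The cost is a few extra items on an online form already in use, one data query, and some additional reports to follow up. Recruitment was due to end on 03/08/2022, so 26-week forms fall due until about the start of February 2023 (3 August plus 182 days). If the form can no longer be changed, step 4 can still be done retrospectively for everyone with CSRI data. Neither the new items nor the CSRI reach families who do not return the forms, and the sample size allows for 30% attrition; the harms report should say so.

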#### Measures routinely used to monitor outcomes in OSI

For the OSI+therapist support arm only, the OSI platform collects routine outcome measures and these will be used to help therapists to evaluate the progress of participants through treatment and to explore the trajectory of participant improvement across the course of treatment. The OSI platform routinely collects the CAIS-P, RCADS-p, SCAS-P8, and ORS as described above, and session rating scales and goal-based outcomes as described below:

Session Rating Scales (SRS): The SRS [42] assesses key dimensions of an effective therapeutic relationship and will be made available for completion at the end of each therapy session to get feedback from the parents so that any issues related to therapeutic alliances can be immediately identified and addressed within treatment. The SRS comprises four simple rating scales in which the parent rates their experience of the treatment session (with regard to relationship with the therapist, goals and topics, approach or method, and an overall rating). It uses the same visual analogue scale as the ORS. It has well-established reliability and validity [42, 43].

Goal-based outcomes (GBOs): This is a simple rating scale in which the parent rates on an 11-point scale (0–10) the extent to which their child has made progress towards up to three treatment goals [44]. Although this measure is now widely used in CAMHS (as part of the CYP IAPT initiative), its psychometric properties have not yet been established.

Routinely collected sessional measures will be used to explore the trajectory of change within the OSI+therapist support arm only to inform future developments of the programme. We will not be collecting routine outcome measures from the treatment as usual arm for comparative purposes as these will vary according to site-specific practice and treatment-specific requirements.

#### Qualitative interviews with parents and therapists

We will conduct qualitative interviews with 20–40 parents and therapists, purposively sampled on the basis of demographic characteristics to explore therapist and parents’ experiences of treating child anxiety problems in the current context. We have previously found that this sample size is sufficient for data saturation. Qualitative interviews will be conducted between 14 and 26 weeks after randomisation. Interviews will be conducted by a qualitative researcher and will be based on a topic guide (see Additional file 1), which will be developed and finalised following consultation with PPI representatives.

We will invite 10 parents and therapists from the first 20 participants to complete treatment to take part in the qualitative interviews and will review their demographics to identify characteristics that have not been represented using a grid developed specifically for this study to identify future participants to invite to take part (i.e. following a purposive sampling approach to ensure diversity among participants). We will initially invite participants to take part in the interview by email and will follow this up with telephone/text messages (up to three times). Interviews will be conducted remotely via Microsoft Teams (Teams) or over the telephone. Interviews will be audio recorded through Teams or an encrypted digital recorder. Recordings will be transcribed by the research team manually or via Teams and then checked/amended for accuracy. Information that could reveal the identity of a participant to other people will not be included in transcriptions. Transcripts will then be uploaded to NVivo [45] for analysis.

### Plans to promote participant retention and complete follow-up {18b}

Families will receive a £10 voucher as a thank you for completing extra questionnaires that they would not usually complete as part of routine care. Furthermore, parents or clinicians who take part in the additional qualitative interview will also receive a £20 voucher.

Shortly after being randomised to their treatment, participants will receive a telephone call welcoming them to the trial, explaining what is involved and answering any initial questions. To further promote participant engagement, families who are active in the study will be emailed a monthly parent bulletin, containing updates about the trial. There will also be a Twitter account that families will be invited to follow. In terms of completing follow-ups, there will be a scheduled series of emails, text messages, and telephone calls made to the families during the 1-month window that their 14-week and 26-week questionnaires are due. These will promote participant retention through reminding the families to complete the questionnaires and assist them with any difficulties they may be having.

Participants who discontinue treatment or deviate from protocol will be contacted by the research team and asked whether they would still be able to complete their follow-up questionnaires. In the event that the family are non-contactable, the research team will continue with the scheduled reminders unless the family state they wish to withdraw fully from the trial. The measures collected from these participants will be the same as per-protocol participants (outlined in Section 18a).

